### Interim analyses {21b}

Not applicable; no interim analysis is planned.

### Methods for additional analyses (e.g., subgroup analyses) {20b}

We plan to conduct a subgroup analysis that compares the *H. pylori* eradication rate between the clarithromycin resistance group and the empirical BQT failure group. Both groups are HDDT treatment regimens; the former is first-line treatment, and the latter is the rescue treatment. We anticipate that HDDT will be equally effective in both groups. A point estimate and a two-sided 95% CI of the difference in eradication rates between the two groups will be calculated via the Miettinen & Nurminen method. Statistical significance will be set at *P* < 0.05.

### Methods in analysis to handle protocol non-adherence and any statistical methods to handle missing data {20c}

The primary and secondary outcomes will be evaluated using ITT, mITT, and PP analyses. Participants who have not undergone a re-examined 13C-UBT will be considered as treatment failures, i.e., ‘not eradicated,’ in the statistical analysis. Strategies will be implemented to maximise follow-up, improve adherence, and prevent missing data. We will report the reasons for non-adherence for each randomisation group and compare the reasons qualitatively.

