### Outcomes {12}

The primary outcome of the study is the proportion of participants with successful *H. pylori* eradication. This will be determined according to the results of 13C-UBTs performed at least 4 weeks after the end of the first-line treatment period between the SGT and ET groups.

The secondary outcomes: The rescue treatment and the overall eradication rates in the SGT and ET groups. The eradication rate of HDDT for the clarithromycin resistance group and the empirical BQT failure group. Frequency of AEs and the rate of compliance between the SGT and ET groups.

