## Data collection and management

### Plans for assessment and collection of outcomes {18a}

Sociodemographic and baseline information (including name, sex, age, contact information, and past medical history) will be collected during screening. The success of *H. pylori* eradication will be assessed using 13C-UBT 4 weeks after therapy completion. Before getting the 13C-UBT done, participants will not be allowed to use any PPIs or antibiotics for 2 weeks and 30 days, respectively. Considering the impact of the COVID-19 pandemic, we require the 13C-UBT to be done at most 8 weeks after the completion of therapy. The information on AEs and compliance throughout the study will be collected via telephone and recorded using the data collection form (Additional file 2) 3 days after the completion of therapy. Study drug compliance will be based on the number of days of drug administration. Because 10-day therapy regimens can achieve good eradication rates [28, 29], 10 or more days will be considered good compliance and less than 10 days bad compliance. Data will be collected by two dedicated data collectors who will be trained in collecting the information in a uniform, reproducible manner, and the quality of the data will be supervised by the principal investigator.

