## Statistical methods

### Statistical methods for primary and secondary outcomes {20a}

The eradication rate of *H. pylori* will be evaluated using ITT, mITT (including all participants who received at least one dose of the study drug), and per-protocol (PP) analyses (including participants who had good compliance and were re-examined by 13C-UBT). A point estimate and two-sided 95% CI of the difference in eradication rates between the SGT and ET groups will be calculated via the Miettinen & Nurminen method for the primary and secondary outcomes. Participants who have not undergone a re-examined 13C-UBT will be considered as treatment failures, i.e., ‘not eradicated,’ in the statistical analysis. Propensity score analysis will be used to adjust for differences in treatment regimens and potential confounding factors. Compliance and sensitivity analyses will be conducted to compare the treatment responses between compliant and non-compliant participants and determine if there is a significant association between compliance and treatment outcomes. Statistical significance will be set at *P* < 0.05.

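### The rule that a missing breath test counts as failure has no stated limits, so it can bias the compliance comparison and, on one reading, the rescue rates

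*Protocol article*

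**What the plan says.** The rule appears in the protocol article under Statistical methods {20a}: "Participants who have not undergone a re-examined 13C-UBT will be considered as treatment failures". It is repeated under {20c}, directly after the sentence "The primary and secondary outcomes will be evaluated using ITT, mITT, and PP analyses". Neither place limits it to an outcome or to an analysis set.

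Section {20a} defines the mITT set as "including all participants who received at least one dose of the study drug" and the PP set as "including participants who had good compliance and were re-examined by 13C-UBT". The same section plans to "compare the treatment responses between compliant and non-compliant participants and determine if there is a significant association" between compliance and outcome, and names no analysis set for this. Compliance is defined under {18a}: "10 or more days will be considered good compliance and less than 10 days bad compliance".

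Outcomes {12} lists among the secondary outcomes "The rescue treatment and the overall eradication rates in the SGT and ET groups". Rescue is described in {6b} and {11a} as following failure of first-line treatment. The text does not separate a failure shown by a positive test from one imputed because the test is missing.

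**The concern.** Counting an untested participant as a failure is a common, conservative rule for an ITT eradication rate. Two of the planned analyses ask a different question.

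- **Compliance and outcome.** This comparison cannot use the PP set, which holds only compliant participants, so by default the imputation applies to it. Under {18a}, compliance is recorded by telephone 3 days after therapy, while the breath test comes 4 to 8 weeks after therapy. A participant can therefore be classed as non-compliant, never be tested, and be scored as a failure. If people who stop their drugs early also skip the test, the rule contributes to the association being tested.
- **Rescue rate.** A participant with no first-line test is a failure under the rule. If that also places the participant in the rescue denominator, someone who never took rescue drugs counts as a rescue failure.

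A reader of the results could then take attendance for testing as an effect of compliance or of rescue treatment. For the primary outcome, no stated analysis shows how much the result depends on the rule.

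**Working it through.** **The plan's own figures.** Sample size {14} assumes 90% vs 80%, 80% power and two-sided alpha 0.05. With unpooled variance, n = (1.960 + 0.842)² × (0.9×0.1 + 0.8×0.2) / 0.1² = 196.2, so 197 per arm. Then 197 / 0.8 = 246.25, so 247 per arm and 494 in all, raised to 500. The stated figures reproduce. The 20% dropout allowance is the only figure in the document that bears on missing tests. It is a planning allowance, not a forecast of missing tests by arm or by compliance.

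**PP set.** Membership requires a repeat test, so the rule changes nothing there.

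**Compliance comparison.** The document gives no true rate by compliance, no share non-compliant and no missingness by compliance. I assume N = 500, 85% true eradication in both groups and 10% non-compliant (450 vs 50). Under the rule, reported rate = 0.85 × (1 − proportion missing).

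| Missing: compliant / non-compliant | Missing overall | Reported rates | Difference (points) |
|---|---|---|---|
| 5% / 5% | 5.0% | 80.8% vs 80.8% | 0 |
| 5% / 20% | 6.5% | 80.8% vs 68.0% | 12.8 |
| 5% / 50% | 9.5% | 80.8% vs 42.5% | 38.3 |
| 15% / 65% | 20.0% | 72.3% vs 29.8% | 42.5 |

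At 5%/20% the chance of P < 0.05 is about 56% by normal approximation. It is about 36% if only 5% are non-compliant (475 vs 25). These chances are rough because the non-compliant group is small. Among tested participants the expected difference is 0 in every row, provided that being tested is unrelated to eradication within each compliance group.

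**Rescue rate, if untested first-line participants are counted.** I take 250 per arm, first-line rates of 80% (ET) and 90% (SGT) among those tested, equal missingness m, equal true rescue success r, and every confirmed failure starting rescue and being tested after it. With p the arm's first-line rate, confirmed failures = 250(1 − m)(1 − p). The reported rescue rate = r × confirmed / (confirmed + 250m).

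| m | r | ET | SGT | SGT deficit (points) |
|---|---|---|---|---|
| 5% | 80% | 38/60 = 63.3% | 19/36.25 = 52.4% | 10.9 |
| 10% | 80% | 36/70 = 51.4% | 18/47.5 = 37.9% | 13.5 |
| 20% | 80% | 32/90 = 35.6% | 16/70 = 22.9% | 12.7 |
| 5% | 90% | 42.75/60 = 71.3% | 21.375/36.25 = 59.0% | 12.3 |
| 10% | 90% | 40.5/70 = 57.9% | 20.25/47.5 = 42.6% | 15.2 |
| 20% | 90% | 36/90 = 40.0% | 18/70 = 25.7% | 14.3 |

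The arm with the better first-line rate is penalised because the same number of untested people is a larger share of its failures. With confirmed failures only, both arms show r and the difference is 0.

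**Primary outcome.** If 90% and 80% are the rates among those tested and 20% are missing in each arm, the ITT rates are 0.9×0.8 = 72% and 0.8×0.8 = 64%. The difference shrinks from 10 points to 8. ITT and mITT both impute failure. PP removes untested and non-compliant participants together, so moving from mITT to PP changes two things at once.

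**The case against.** Several points on the other side stand.

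- A reader might infer that the rule distorts every analysis. It does not. PP excludes untested participants by definition, and adverse event frequency and the compliance rate are not eradication outcomes.
- A reader might infer that the rule by itself produces the compliance result. With equal missingness the bias is zero. The missingness figures are assumptions, and the 15%/65% row is an extreme one. The analysis is also exploratory.
- A reader might infer that the rescue comparison will be biased against SGT. That needs people who never took rescue drugs to be in its denominator, which the document does not say. Sections {6b} and {11a} describe rescue as treatment given after failure. Section {20b} treats the group failing empirical quadruple therapy as receiving dual therapy. The mITT condition of one dose could be read as one rescue dose. These passages point away from the damaging reading, though taken literally anyone with a first-line dose qualifies for mITT.
- A reader might infer that the primary analysis is unsound. The rule is fixed in advance and identical in both arms, and with equal missingness it dilutes the difference. A reversal needs unequal missingness of a size with no source in the document. For example, 25% untested in SGT and 15% in ET gives 0.9×0.75 − 0.8×0.85 = −0.5 points, but the opposite split gives 0.9×0.85 − 0.8×0.75 = +16.5. Participants lost before dosing leave the mITT set, so ITT against mITT covers that route.

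It can also be said that denominators and sensitivity analyses belong in an analysis plan that is not shown. That would answer a complaint about silence. Here the protocol states the rule, twice and without limits, and plans a comparison to which the rule is ill suited.

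**Conclusion.** The concern holds in a limited form. As written, the rule reaches the compliance comparison, because that comparison cannot be done in PP and no other set or exception is named. It can create an association where none exists, from 0 points with equal missingness to about 13 points at 5%/20% and about 43 points at 15%/65%. These figures assume 85% true eradication in both groups and 10% non-compliant.

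For the rescue rates the effect is conditional. A spurious SGT deficit of about 11 to 15 points arises at 5% to 20% missing and 80% to 90% true rescue success, but only if untested first-line participants are counted. The text leaves this open, and its descriptions of rescue lean against it.

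For the primary and overall ITT and mITT rates the rule is acceptable. What is lacking is an analysis that varies the missing-test assumption on its own.

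**What to change.** 1. State that missing counts as failure for the primary and overall eradication rates in ITT and mITT.
2. Run the compliance-outcome comparison only in participants with a breath test result, and label it observational.
3. Base the rescue rate on participants with a UBT-confirmed first-line failure who start rescue, and report it per arm with confidence intervals. This subset is selected after randomisation, so use the overall rate on all randomised participants as the between-arm comparison.
4. Add a sensitivity analysis of the primary outcome that varies eradication among untested participants separately by arm.

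The cost is a few sentences, a few extra tables, and smaller denominators for the rescue and compliance analyses. No additional data collection is needed.

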### Plans to give access to the full protocol, participant-level data, and statistical code {31c}

We will deliver a completely deidentified data set to an appropriate data archive for sharing purposes within 1 year after the study completion.

## Oversight and monitoring

### Composition of the coordinating centre and trial steering committee {5d}

The principal investigator is the designer of the trial and is responsible for conducting the study. The principal investigator and research physicians are responsible for the recruitment, treatment, follow-up of study participants, severe AEs, and serious unexpected suspected adverse events (SUSAR) reports. The Data Manager will be responsible for data collection, data entry, and data verification. A steering committee will be set up to supervise the entire study process. The study team will meet every two weeks to monitor the study’s conduct. Frequent contact via WeChat and telephone will ensure that the study runs smoothly.

### Composition of the data monitoring committee, its role and reporting structure {21a}

No data monitoring committee will be established because the trial has a short duration, and the treatment regimens are associated with known, minimal risks.

### Adverse event reporting and harms {22}

In this study, we will monitor for treatment-emergent AEs, which are defined as any events that occur after the administration of the first dose of a study drug, or any events at baseline that worsen in either intensity or frequency after the first dose of the study drug. An adverse event that meets the criteria for a serious adverse event will be reported to the Ethics Committee of Liaocheng People’s Hospital.

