### Intervention description {11a}

The SGT group’s regimens will be selected according to *H. pylori* susceptibility to clarithromycin and levofloxacin. Participants will undergo an upper endoscopy to provide gastric mucosal samples for molecular testing. The test is based on polymerase chain reaction (PCR), which detects *H. pylori* mutations associated with clarithromycin and levofloxacin resistance. The susceptibility testing PCR protocol is outlined in Additional File 1. Regimens for the first-line treatments are based on clarithromycin susceptibility: If the *H. pylori* strain is sensitive to clarithromycin, we will administer clarithromycin triple therapy—esomeprazole (20 mg, twice daily), clarithromycin (500 mg, twice daily), and amoxicillin (1.0 g, twice daily)—for 14 days, as per the recommended guideline [17]. If the strain is clarithromycin resistant, we will administer the HDDT regimen because a network meta-analysis revealed that this treatment is the most optimal first-line therapy for *H. pylori* among the Asian population [24]. If the first-line treatment fails, rescue therapy will be selected according to levofloxacin susceptibility. If the *H. pylori* strain is levofloxacin sensitive, we will administer the levofloxacin quadruple regimen—esomeprazole (20 mg, twice daily), levofloxacin (500 mg, once daily), amoxicillin (1.0 g, twice daily), and colloidal bismuth pectin (150 mg, four times daily)—for 14 days, as per the recommended guideline [17]. If *H. pylori* is levofloxacin-resistant, we will administer the furazolidone quadruple regimen—esomeprazole (20 mg, twice daily), furazolidone (100 mg, twice daily), amoxicillin (1.0 g, twice daily), and colloidal bismuth pectin (150 mg, four times daily)—for 14 days. This furazolidone regimen can provide a satisfactory eradication rate in patients with multiple treatment failures and does not increase the incidence of adverse events [25, 26].

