### Plans for collection, laboratory evaluation and storage of biological specimens for genetic or molecular analysis in this trial/future use {33}

The investigators will obtain gastric mucosal biopsy specimens for antimicrobial susceptibility testing. Two biopsy specimens will be obtained from each patient: one from the greater curve of the antrum and one from the lesser curve of the gastric body. The specimens, which are marked with unique patient identifiers, will be kept in only one refrigerator at -28 °C, and maintained by a specimen administrator who will keep the refrigerator key. ShunFeng EXPRESS will transfer the specimens to Zhiyuan Medical Inspection Institute Co., Ltd. (Hangzhou, China) every 3 days using a drikold delivery box. A standard protocol will be used for the biopsy, storage, and transfer processes. The *H. pylori* and genotypic resistance statuses of each patient will be revealed by PCR testing, which will help detect the presence of mutations conferring resistance to clarithromycin and levofloxacin.

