The limitation of our study is that to obtain gastric biopsies for susceptibility testing, we require endoscopies, which are expensive, uncomfortable, and have a low acceptance rate by patients. Further studies into the development of more easily accessible methods of resistance testing, such as stool testing for the six commonly used antibiotics without the need for endoscopy, are required.

In summary, this randomised controlled trial will provide objective and valid evidence about the value of PCR-based molecular methods used for AST in guiding *H. pylori* eradication.

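### Adverse events are counted only from the first drug dose, so harms of the study endoscopy that start earlier and do not worsen after dosing drop out of the between-arm safety comparison

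*Protocol article*

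**What the plan says.** The only AE definition in the protocol article is under Adverse event reporting and harms {22}. It covers treatment-emergent events, "defined as any events that occur after the administration of the first dose of a study drug". Its single extension is to "any events at baseline that worsen in either intensity or frequency after the first dose of the study drug". The same section sends serious adverse events to the Ethics Committee, in a sentence that does not mention the first dose.

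Outcomes {12} lists as a secondary outcome "Frequency of AEs and the rate of compliance between the SGT and ET groups".

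Intervention description {11a}, within its account of the SGT group, states: "Participants will undergo an upper endoscopy to provide gastric mucosal samples for molecular testing". It then says: "Regimens for the first-line treatments are based on clarithromycin susceptibility". The section on biological specimens {33} is not limited to one arm: "Two biopsy specimens will be obtained from each patient: one from the greater curve of the antrum and one from the lesser curve of the" (the sentence ends by naming the body of the stomach). Specimens go to an outside laboratory in shipments three days apart.

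AEs and compliance are collected by a telephone call three days after treatment ends (Plans for assessment and collection of outcomes {18a}). The form used conceals the allocation, so that data collectors stay blinded (Who will be blinded {17a}).

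**The concern.** A window that opens at the first dose suits a comparison of drug regimens. This trial compares two strategies, and one of them contains an invasive test. Eligibility criteria {10} admit patients on a breath or stool test alone, so entry does not require endoscopy. The Discussion names the procedure as the cost of the guided approach: "we require endoscopies, which are expensive, uncomfortable, and have a low acceptance rate by patients". The safety outcome as defined cannot register that cost when it falls before dosing.

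What is at stake is a declared secondary outcome. A reader of the final AE table would take it as the harm of one strategy against the other, when it would show harm from the first tablet onward.

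**Working it through.** There is no stated figure to reproduce. The check is one of sequence, and the plan's sections fix most of it.

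1. Consent comes before any study procedure (Who will take informed consent? {26a}).
2. The SGT participant has an endoscopy with two biopsies ({11a}, {33}).
3. Specimens are stored, shipped and tested by PCR ({33}). With shipments three days apart, the gap before dosing can run to days.
4. The clarithromycin result selects the first-line regimen ({11a}).
5. The first dose is given. The AE window in {22} opens here.
6. The AE call is made three days after treatment ends ({18a}).

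Steps 2 to 4 lie inside trial participation and outside the window. Applying the definition in {22} to each kind of procedural event:

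- starts and resolves before the first dose: not counted;
- starts before the first dose and persists without worsening: not counted;
- starts before the first dose and worsens afterwards: counted;
- starts after the first dose, whatever its cause: counted;
- occurs in a participant who is never dosed: not counted. There is also no end of treatment from which to time the call.

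The last case also shows that the populations differ. The intention-to-treat analysis of eradication would keep a never-dosed participant, while the AE definition cannot record an event for that person.

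The direction depends on who is biopsied, and the protocol can be read two ways:

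- Only SGT has the study endoscopy (the natural reading of {11a}): uncounted events fall in SGT alone, and the AE comparison favours SGT.
- Every participant has it (the literal reading of {33}): the omission applies to both arms and does not bias the difference, but procedural harm is under-counted throughout.

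On size, Sample size {14} aims for 500 participants and Trial design {8} gives 1:1 allocation, so 500 / 2 = 250 per arm. Let p be the proportion with a pre-dose procedural event that does not worsen after dosing. The number missed is 250 × p on the first reading and up to 500 × p on the second. The documents give no value for p. Each percentage point is 250 × 0.01 = 2.5 participants in SGT, or 500 × 0.01 = 5 if all are biopsied.

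**The case against.** The strongest reply has four parts.

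First, a treatment-emergent window is a common convention, and a journal article condenses the full protocol. The schedule figure and the AE form (Additional File 2) are not shown, and either might provide for procedural events. This limits what can be said about the form. It does not remove the point, because {22} states an explicit rule and that rule excludes these events.

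Second, a reader might infer that no endoscopy harm is ever captured. That is too strong: an event that begins or worsens after the first dose counts, whatever its cause.

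Third, a reader might infer that serious procedural events also escape reporting. The text does not support this. The serious-event sentence is not tied to the first dose, {18a} speaks of AEs over the whole study, and the steering section {5d} gives the investigators responsibility for severe events without a dosing limit. Such an event may well reach the Ethics Committee. It still would not enter the treatment-emergent count.

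Fourth, a reader might infer that the comparison certainly favours SGT, or that the endoscopy certainly follows allocation. Neither is established. The specimen section refers to each patient, and no section places the endoscopy before or after the allocation call. Some participants recruited in the endoscopic centre may also be having an endoscopy for clinical reasons, which reduces the number of added procedures.

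These replies narrow the point to pre-dose events that do not worsen, and make the bias conditional. They leave the gap in the definition in place.

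**Conclusion.** The concern holds in this bounded form. The stated AE window opens after a procedure that belongs to the SGT strategy, so pre-dose procedural events that do not worsen afterwards, and those in never-dosed participants, are missing from the secondary AE comparison. This follows from the text and needs no assumed event rate. Bias towards SGT rests on the assumption that ET participants do not have the study endoscopy; if they do, the effect is under-counting without bias from this source.

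The number of missed events is unknown. The documents give no procedural complication rate and do not mention sedation, so neither a projected count nor a list of sedation harms would have a basis in them.

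The primary eradication outcome, the sample size and the efficacy analyses are untouched. The change is worth making because it is small and a declared outcome is incomplete without it.

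**What to change.** In Adverse event reporting and harms {22}:

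- Start AE and SAE recording at consent or randomisation, the same in both arms. Because the order of endoscopy and allocation is not stated, the starting point chosen must come before the study endoscopy; consent does so in either case.
- Keep treatment-emergent AEs as a sub-category, so the planned drug comparison is still available.
- Report pre-dose and procedure-related events by randomised arm, in all randomised participants, beside the treatment-emergent figures.
- State which arms have the study endoscopy, so that {11a} and {33} agree and the comparison can be interpreted.

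The unblinded investigators should record pre-dose events at or before drug dispensing, or at withdrawal if the participant is never dosed. A face-to-face session at first dispensing is already planned (Strategies to improve adherence {11c}). These events should not go on the telephone form. If only SGT has the endoscopy, a procedure item there could reveal the arm to the blinded collectors, and a call timed from the end of treatment would miss never-dosed participants.

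The cost is a little more recording work and SGT AE figures that may look slightly less favourable. Pre-dose events would be recorded unblinded, which is a further reason to show them separately. No treatment, sample size or efficacy analysis changes.
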